#### Adverse events

To investigate treatment safety, we will perform an exploratory comparison of rates of adverse events between the OLP group and the no-treatment group. Individual baseline symptoms will be considered when interpreting the results.

#### Role of expectations

To investigate whether positive expectations amplify beneficial effects of the OLP treatment, value expectations, probability expectations, and optimism are separately included in the primary outcome models as candidate moderators. The interaction effect time × group × expectation variable will be tested with significant effects indicating that expectation moderates group effects. The trajectory of value and probability expectations over time will also be subject to exploratory analysis.

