**Fig. 1 Fig1:**
[figure not shown]
Schedule of enrolment, intervention, and assessment according to SPIRIT. *Post* post-treatment, *wk* week, *FU* follow-up, *OLP* open-label placebo, *HFRS* Hot Flush Rating Scale, *WHQ* Women’s Health Questionnaire, *PGIC* Patient Global Impression of Change, *MRS* Menopause Rating Scale, *MHQ* Menopause Health Questionnaire, *AUDIT-C* Alcohol Use Disorders Identification Test—Consumption, *PHQ* Patient Health Questionnaire, *PSS* Perceived Stress Scale, *LOT-R* Life Orientation Test—Revised, *GASE* Generic Assessment of Side Effects. Hot flushes are assessed ambulatory via the hot flush diary. *At baseline, health-related quality of life and expectations are assessed before and after the allocation, respectively. ^†^The fourth study visit and the 8-week follow-up assessment takes place for the OLP 8wk and OLP 4wk groups only. ^‡^For the second allocation, the OLP group is further divided into the OLP 8wk and the OLP 4wk groups. ^§^The interview is conducted at week 8 or later

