### SV 2: Baseline—allocation

At the second study visit, patients are informed about their assignment by a clinician. Clinicians are not aware of the group assignment until the patient has opened the envelope and disclosed the allocation result. Clinicians instruct the OLP group to take two pills a day for 4 weeks, each morning and evening after a meal. A total number of 56 pills are handed out in paper packaging which includes the pill bottle and the original medication leaflet of the producing company. The bottle shows the name of the pill (“placebo”), the number of pills and its equivalent in grams, a subtitle (“for menopausal hot flushes”), the contact data of the responsible party (“Department of Psychosomatic Medicine and Psychotherapy”) and further instructions regarding the pills (e.g. “Store inaccessible to children”). Women are reminded about the importance of taking the pills faithfully and a 50% chance of continuing the treatment for another 4 weeks. Women assigned to the no-treatment group are reminded of the meaning of this study group. The duration of the second study visit is 5 to 10 min.

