### Blinding

Due to the nature of the study, patients and clinicians are aware of group assignment. Assessors are blinded to group assignment of participants. To prevent the breaking of blinding, participants are requested to not communicate their group affiliation when they have questions about the assessments.

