#### Expectations

Participants’ (1) value expectations or hopes/wishes/desires about the treatment, (2) probability expectations, and (3) dispositional expectations, i.e., optimism, are assessed. Due to the lack of validated questionnaires in the field of expectations [58], we created two items (value expectations: “What change would you like to happen to your hot flushes over the next 4 weeks?”; probability expectations: “How do you expect your hot flushes to change over the next 6 weeks?”) which are rated on a scale from 0 (*no change*) to 10 (*maximum improvement*). These items are based on a qualitative interview study with lower back pain patients [59]. We assess optimism with the Life Orientation Test-Revised (LOT-R) [60]. Optimism might constitute a predictor of placebo response, although evidence remains mixed [61, 62].

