## Discussion

This trial is the first to investigate the efficacy of non-concealed placebos for hot flushes among menopausal women. In a randomized-controlled design, we compare 4 weeks of twice daily OLP intake with no treatment. By subsequently dividing the treatment group into two subgroups (continuing vs discontinuing treatment), we will explore the question of how long OLP effects last and whether beneficial effects can be maintained after treatment is discontinued. Additionally, subjective experiences with the placebo treatment are examined by qualitative analysis of participant interviews. Our aim is to uncover whether beneficial effects of double-blind placebos in hot flush trials may also apply to their open-label surrogate [69].

Presumably, the biggest question for OLP is why it works. In the tradition of placebo research, expectations, conditioning, and the patient–practitioner relationship have been suggested as underlying mechanisms [70, 71]. Expectations, i.e., beliefs about future outcomes, are the only potential mechanisms which have been examined as part of OLP studies. The positively framed rationale about placebos may act as a verbal suggestion which enhances positive expectations. One study showed that OLP administration with or without the briefing did not result in differing allergic symptoms [33], whereas another study with healthy participants did find divergent analgesic effects depending on the briefing [34]. Interestingly, in the latter study, expected pain did not differ between the groups. We also assess expectations in both groups to compare whether they differ after allocation and whether they predict the outcome.

Conditioning is based on prior treatment experiences and occurs when neutral stimuli and active treatment are repeatedly paired (associative learning). Since OLP studies did not incorporate conditioning paradigms, the magnitude of conditioning and whether it plays a role cannot be determined. Previous studies included clinical samples which, based on results of qualitative studies, most probably experienced treatment disappointments which would render the conditioning hypothesis contradictory to the beneficial effects of OLP [71].

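### Value and probability expectations are rated after the woman knows her arm, so a significant interaction with group does not by itself show that expectation moderates the effect

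*Protocol article*

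**What the plan says.** All places are in the protocol article.

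- **Timing (Fig. 1 legend):** "At baseline, health-related quality of life and expectations are assessed before and after the allocation, respectively". Quality of life comes first and expectations come after allocation.
- **Knowledge of the arm (SV 2: Baseline—allocation; Blinding):** "At the second study visit, patients are informed about their assignment by a clinician", and "patients and clinicians are aware of group assignment".
- **Use (Role of expectations):** "value expectations, probability expectations, and optimism are separately included in the primary outcome models as candidate moderators".
- **Inference rule (same section):** "The interaction effect time × group × expectation variable will be tested with significant effects indicating that expectation moderates group effects".
- **Possible effect of allocation on the ratings (Discussion):** "We also assess expectations in both groups to compare whether they differ after allocation and whether they predict the outcome". The same paragraph names expectations among the suggested mechanisms of open-label placebo (OLP).
- **Item wording (Expectations):** the value item asks about the coming 4 weeks. The probability item reads "How do you expect your hot flushes to change over the next 6 weeks".

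The text describes no rating of the value or probability item before allocation. The grid of Fig. 1 was not available to me. If it shows an enrolment rating of these items, that rating could serve as the moderator, and the protocol should say so.

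**The concern.** A moderator divides women by something that was settled before treatment was assigned. The value and probability ratings do not meet that condition, because each woman gives them knowing whether she will receive pills. For the probability item the difficulty is concrete. A woman just told that she is untreated can rate only the natural course. A woman handed pills rates the natural course plus whatever she believes the pills will do. The same score can then mean different things in the two arms, and its relation to outcome can differ by arm with no moderation at all.

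The protocol also treats the same variable in two ways: as something allocation may alter (Discussion) and as a moderator of allocation (Role of expectations). At stake is one of the further questions at the end of the Background, namely whether benefit is related to positive expectations. A significant term would be reported as amplification of the placebo effect when other explanations remain open.

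**Working it through.** **1. Order of events.** The envelope is opened at the start of visit 2 (Randomization), the woman learns her arm there, and the baseline expectation items follow. The placebo briefing was given to everyone at visit 1, before randomisation. A rating after the briefing but before the envelope was therefore feasible.

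**2. The plan's own figures.** The protocol gives none for this analysis. The sample size supplies the number per arm. A two-sided t-test at 0.05 with 45 per arm and d = 0.60 has power 80.4%, and 90 / 0.9 = 100, so the stated 90 and 100 reproduce.

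**3. When does a post-allocation rating create an interaction?** Take a simple model in SD units, with assumed values that are not in the protocol. E0 is the pre-allocation expectation, U is perceived prognosis (independent of E0), and A = 1 for OLP.

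- Rating after allocation: E1 = √(1 − λ²)·E0 + λ·U + shift·A, with λ allowed to differ by arm.
- Outcome: Y = −0.6·A − 0.5·U − m·A·E0 + noise, where m is the true moderation.

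E1 has variance 1 within each arm, so the group × rating coefficient is

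−0.5·(λ_OLP − λ_none) − m·√(1 − λ_OLP²).

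With m = 0 (no moderation), 45 per arm and 4000 runs:

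| λ OLP / none | Shift | Formula | Simulated coefficient | Rejected at 0.05 |
|---|---|---|---|---|
| 0 / 0 | 0 | 0 | 0.006 | 5.2% |
| 0 / 0 | 1 SD | 0 | 0.002 | 4.6% |
| 0.6 / 0.6 | 1 SD | 0 | 0.003 | 5.5% |
| 0.3 / 0 | 1 SD | −0.5 × 0.3 = −0.15 | −0.153 | 10.3% |
| 0.6 / 0 | 1 SD | −0.5 × 0.6 = −0.30 | −0.301 | 28.9% |
| 0.8 / 0 | 1 SD | −0.5 × 0.8 = −0.40 | −0.398 | 47.3% |

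The pre-allocation rating E0 rejects in 4.6% to 5.7% of runs throughout.

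**4. If moderation is real (m = 0.5).** E0 gives about −0.50 with power about 63%. The post-allocation rating gives:

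- λ 0.6 / 0: −0.5 × 0.8 − 0.5 × 0.6 = −0.70, power 92%
- λ 0 / 0.6: −0.5 + 0.5 × 0.6 = −0.20, power 15%
- λ 0.8 / 0.8: −0.5 × 0.6 = −0.30, power 34%

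The error can go in either direction.

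**5. Closer to the planned model.** Steps 3 and 4 use a two-way term on one post-treatment score. The plan tests a three-way term with time, in a model that also has the baseline score as covariate. A second set of assumptions was used for this: 45 per arm, effect −6 points, no moderation, a disposition correlated 0.3 to 0.5 with outcome, and no-treatment ratings with 30% to 50% of the spread of OLP ratings.

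- Unadjusted post-treatment score: 12% to 52% rejection.
- Change from baseline or baseline-adjusted score, disposition reflecting stable severity: about 4% to 17%.
- The same, disposition predicting change: about 15% to 69%.
- Constant 2-point drop with equal spread: near 5%.

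The ranges also move with the assumed correlation between baseline and post-treatment scores. At correlations of 0.5 to 0.7, the stable-severity case ran up to 27% for adjusted scores, and the predicts-change case up to 82% for change scores.

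**The case against.** The strongest reply is that the simulated rates rest on invented inputs. Nothing in the protocol says that knowing the arm changes the spread or meaning of the ratings. If allocation leaves them alone, shifts them uniformly or acts equally in both arms, the test keeps its 5% level. That is correct, and it is why no percentage can be quoted as the error rate of this trial. But a comparison of mean ratings between arms would not reveal whether the condition holds, because it concerns what the ratings reflect. A rating taken before allocation avoids having to assume it.

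The reach is also limited, and this stands in full. The analysis is listed among further research questions, with candidate moderators. Optimism on the LOT-R is a disposition that allocation should hardly change. The Background asks only whether benefit is related to expectations, and the Discussion whether expectations predict outcome. Post-allocation ratings can inform both. The fault lies in one rule of interpretation.

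A further reply is that a pre-allocation rating measures something else: expectation averaged over an even chance of treatment, not expectation under a known open-label placebo. That is true, and it is a reason to keep the later rating as well. It does not make the later rating a moderator.

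A reader might infer that the treatment effect itself is distorted, since the group coefficient at equal expectation is no longer the randomised contrast. The documents do not support that worry. The efficacy model contains no expectation variable, and the moderator section interprets only the interaction.

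**Conclusion.** The point holds for the value and probability items. They are rated after the arm is known, the protocol allows that allocation may change them, and a significant interaction is nevertheless to be read as moderation. Mediation, or a rating that tracks prognosis differently by arm, could produce the same result.

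It would go too far to say that the analysis can never reflect moderation, or that its false-positive rate is 12% to 52%. The first ignores the cases where the test stays valid. The second comes from a two-way term on an unadjusted score under assumed spreads, which is not the planned analysis. The simulations show that the error is possible, and that it needs an arm-specific change in what the rating reflects. They do not show its size here.

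Optimism is largely outside the criticism, and the primary efficacy result is unaffected. The 6-week horizon of the probability item, against 4 weeks for the value item and the outcome, is a separate minor inconsistency and does not carry the argument. The point should be corrected but does not threaten the trial's main conclusion.

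**What to change.** 1. For women still to be enrolled, also ask the value and probability items at visit 2 before the envelope is opened. Use those answers, with LOT-R optimism, as the moderators.
2. Keep the post-allocation ratings for mediation or descriptive analysis.
3. For women with post-allocation ratings only, replace the conclusion attached to the three-way term with a statement of association, or report prediction of outcome within the OLP arm.
4. State in the Role of expectations section which rating, by time point, enters each model.
5. Separately, reconcile the horizon of the probability item with that of the value item and the 4-week outcome. If the item has to stay as it is, report it with its own time frame.

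The cost is two short items a few minutes earlier at an existing visit, plus changes of wording. The drawback is real: recruitment is under way, so the pre-allocation rating will exist for only part of a planned 100 women, and it measures expectation before the arm is known. A moderation test on that subset will have less power than one on the full sample. If few women remain to be enrolled, the change of wording alone removes the unsound inference.

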#### Qualitative analysis

According to IPA procedures, transcripts are analyzed line-by-line to find emerging themes of each participant. Themes are then clustered within patients and compared between patients. The first two interviews will be transcribed and analyzed soon after execution by two researchers. Notes and themes are compared and discrepancies discussed. Further interviews are analyzed by the researchers independently.

## Discussion

This trial is the first to investigate the efficacy of non-concealed placebos for hot flushes among menopausal women. In a randomized-controlled design, we compare 4 weeks of twice daily OLP intake with no treatment. By subsequently dividing the treatment group into two subgroups (continuing vs discontinuing treatment), we will explore the question of how long OLP effects last and whether beneficial effects can be maintained after treatment is discontinued. Additionally, subjective experiences with the placebo treatment are examined by qualitative analysis of participant interviews. Our aim is to uncover whether beneficial effects of double-blind placebos in hot flush trials may also apply to their open-label surrogate [69].

Presumably, the biggest question for OLP is why it works. In the tradition of placebo research, expectations, conditioning, and the patient–practitioner relationship have been suggested as underlying mechanisms [70, 71]. Expectations, i.e., beliefs about future outcomes, are the only potential mechanisms which have been examined as part of OLP studies. The positively framed rationale about placebos may act as a verbal suggestion which enhances positive expectations. One study showed that OLP administration with or without the briefing did not result in differing allergic symptoms [33], whereas another study with healthy participants did find divergent analgesic effects depending on the briefing [34]. Interestingly, in the latter study, expected pain did not differ between the groups. We also assess expectations in both groups to compare whether they differ after allocation and whether they predict the outcome.

Conditioning is based on prior treatment experiences and occurs when neutral stimuli and active treatment are repeatedly paired (associative learning). Since OLP studies did not incorporate conditioning paradigms, the magnitude of conditioning and whether it plays a role cannot be determined. Previous studies included clinical samples which, based on results of qualitative studies, most probably experienced treatment disappointments which would render the conditioning hypothesis contradictory to the beneficial effects of OLP [71].

The patient–practitioner relationship is an important contextual factor which has a small but significant effect on outcomes across diseases [72]. Since patient–practitioner interactions in OLP studies are warm and attentive [28, 30], it may contribute to OLP effects. However, since both groups are kept “constant” considering the relationship, it is unlikely that OLP effects are explicable by the relationship only [71].

An often discussed model for placebo effects is the predictive coding model [73–75]. According to this approach, the brain does not simply process incoming, bottom-up signals. So-called priors, i.e., predictions generated by the brain, affect perception directly, thus resulting in diverging ‘real-world’ perceptions between people. Those predictions are based on the “integration of sensory inputs, prior experience, and contextual cues” (p.1 in [75]). In analogy to Bayesian models, the brain aims to minimize the mismatch between descending priors and ascending signals. If a prediction error occurs, priors are changed accordingly, thus allowing for effective navigation through the world. Notably, priors and signals can take on different degrees of precision. It is argued that strong priors with high precision in combination with vague signals can lead to perceptions corresponding with the priors [74]. Kirsch [76] suggests that given most bodily signals in chronic disease are ambiguous, priors tend to act as self-fulfilling prophecies with regard to symptoms. Importantly, they may or may not be consciously accessible. The role of nonconscious processes is corroborated by recent experiments of Jensen et al. showing that placebo effects can be both acquired (with conditioning) and triggered using subliminal cues (for review, see [77]). Consciously accessible priors would constitute expectations [78].

As pointed out by Wiech [79], having utmost strong and precise (positive) priors might be detrimental since it creates a divergence between prediction and input which undermines the function of minimizing error. Kaptchuk [71] has put forward that, in chronic conditions that fluctuate over time, such as hot flashes, highly precise and strong priors would lead the brain to interpret variations as being just more hot flashes. OLP efficacy may involve introducing its own form of therapeutic uncertainty that shakes up those priors. In previous OLP studies, participants were not simply confident about symptom improvement under placebo. This finding aligns with the results of qualitative studies. For example, patients undergoing acupuncture treatment [80], or blind placebo treatment [81], reported not wanting to expect too much. Subsumed under “the paradox of hope”, this framework describes a balancing act between having enough hope to undergo potentially helpful treatment but refraining from overly positive expectations in order to avoid disappointment [82]. With placebos being widely acknowledged as non-efficacious, patients could preserve some skepticism towards OLP, even when a rationale is provided. However, the uncertainty—in combination with the hope for improvement or desire of relief as it is named in other studies [83]—may generate imprecise but positively toned priors which might have facilitated perception in favor of those priors [70].

Due to the small number of trials, we have confined ourselves to an overview of the proposed mechanisms. Unlike the traditional picture, it is likely that these mechanisms are not mutually exclusive but rather comprise an integrative framework. Further studies are warranted to examine the aforementioned mechanism hypotheses.

### Limitations

There are several limitations and unaddressed questions in our study. One of these is whether OLP generates physiological changes. Two recent experimental OLP studies on healthy people found no effect of OLP on objective parameters [35, 84]. Also, placebo effects in clinical trials across diseases [85], as well as specifically in hot flush trials [86], are known to be caused or amplified by a subjective reporting bias. The physiological measurement of hot flushes is compounded by the circumstance that concordance rates between self-rated and physiological measures are low [47, 87], which renders an interpretation of its dissonance difficult. Although limitations are present, the ambulatory assessment of symptoms minimizes potential biases like memory and emotions. The diary is also the gold standard for hot flush assessments, which allows for comparison with other studies.

Another limitation is a possible self-selection bias. In postings, we will describe our treatment as a novel “mind-body treatment”. This might attract women who are particularly open to alternative and complementary treatments. However, as discussed by Kaptchuk et al. [30] and Kelley et al. [31], self-selection also occurs in clinical practice, i.e., patients are given recommendations by the practitioner and thereby also the choice of accepting or declining treatments. The previous use of hormonal or non-hormonal treatments is assessed in this study to further explore this discussion point.

